## Methods/design

This study is funded by the Canadian Institutes of Health Research (CIHR). The protocol has received ethics approval from the Hamilton Integrated Research Ethics Board (HiREB), the St. Joseph’s Care Group Research Ethics Board, the North York General Hospital Research Ethics Board, and the Southlake Regional Health Centre Research Ethics Board. The fourth participating site, Canadian Mental Health Association – Waterloo Wellington, does not have an internal ethics review board, but the protocol was approved by their Quality and Risk, and Privacy departments.

### Virtual study communication and data collection

All communication and data collection will be done virtually using Zoom Healthcare (HIPAA/PHIPA-complaint videoconferencing software), telephone, e-mail, online surveys (Qualtrics), and SignNow. This will be done to mitigate any in-person contact due to COVID-19 social distancing regulations, as well as to reduce barriers to participation related to geography.

### Study design

We will use a multi-site case study with a mixed method pre/post design [37] to examine our implementation approach. We will collect quantitative measures evaluating therapist adherence to key components of FBT, therapist fidelity to the vFBT model, therapist change in readiness, attitudes, and confidence in implementing vFBT over time, and patient outcomes (changes in weight and binge/purge frequency). Qualitative data will be collected using virtual focus groups and interviews to understand implementation team and patient/family experiences of vFBT.

### Setting

We will work with four pediatric ED programs affiliated with the Ontario Community Outreach Program for Eating Disorders (OCOPED; led by GM), who provide psychotherapeutic intervention to children and adolescents under the age of 18 years. These four participating organizations (from a potential 22 organizations within OCOPED) voiced their interest, readiness, and capacity to implement vFBT in our preparatory work for this project.

### Eligibility criteria

#### Therapists, medical practitioners, and program administrators

To participate in this study, these individuals must work in Ontario, Canada, have the ability to read, understand, speak, and write in the English language and have access to a working computer/electronic device with a stable internet connection. Specifically, therapists must have prior training and supervision in standard FBT and be actively delivering FBT within their treatment programs. Medical practitioners must either be doctors (MD) or nurse practitioners (NP). Program administrators must currently manage an ED program.

#### Patients

To participate in this study, patients must be under 18 years of age; have a diagnosis of Anorexia Nervosa; live in Ontario, Canada; have the ability to read, understand, speak, and write in the English language; and have access to a working computer/electronic device with a stable Internet connection.

### Sample size

The four ED programs participating in the study average two therapists per program, yielding an approximate sample size of eight therapists, four medical practitioners, and four program administrators. We are aiming to recruit one family with an eligible patient per therapist at each site (eight families total). Although a sample size calculation was not completed, we believe this is an appropriate sample size for a feasibility study with this population.

### Procedures and timelines

#### Completed previously: phase 1—initial considerations regarding the host setting

Our implementation approach will follow the stages identified by the QIF [33]. Phase 1 site engagement and buy-in has been completed, by virtue of a well-established network that worked together on previous implementation studies. Of the four ED programs that voiced interest and capacity in implementing vFBT, two programs participated in our prior implementation study. The other two sites have subsequently received training in standard FBT through OCOPED training events. Also, during this time (pre-funding), we identified (with vFBT model co-developer JL) the types of adaptations required for virtual delivery in vFBT to ensure they do retain the key components of the standard FBT model, as these are essential for treatment effectiveness. These adaptations are summarized with the Framework for Reporting Adaptations and Modifications – Enhanced (FRAME) [38] in mind in Table 1.

**Table 1 Tab1:** Adaptations to family-based treatment (FBT) for virtual delivery

Component of FBT	What is the adaptation?	Why was the adaptation made?	Was the adaptation planned or unplanned?	What are the implications for fidelity?
**Weighing**	Therapist weighs patient virtually with patient at home instead of in clinic (home scale is required).	Patient is unable to come into the clinic for in-person visits.	Planned (proactive adaptation).	The patient’s weight is captured as intended. The process of weighing is maintained.
**Time spent alone with adolescent**	Parents are asked to leave the room for the first 10 min of the session so that individual time can be spent between the adolescent and therapist.	In a clinic setting, the adolescent is taken from the waiting room. In virtual therapy, family members often come on screen together, so parents must be asked gently and respectfully to leave.	Planned (proactive adaptation).	Time spent alone with adolescent is maintained.
**Sharing the weight graph**	Therapist plots the weight graph and shares it over the screen by holding up the sheet of paper. Weight graph is reviewed together virtually. The graph could also be plotted electronically by therapist and they could use the “share screen” feature.	Usually the graph is easily shared in person. Virtually, it can be difficult for the family to see the graph on paper; therefore, using the “share screen” feature can be helpful.	Planned (proactive adaptation).	The weight graph is shared and reviewed as intended.
**Family meal**	Family meal (observed by the therapist) is completed virtually, with the ability of parents to gather additional food items if needed (since they are in their own homes).	When done in person, the option of additional food items is limited. With the family at home they have many more options available to them.	Planned (proactive adaptation).	Family meal is conducted as intended.
**Therapeutic principles**	All sessions are to be completed virtually and with the same principles as in-person treatment with emphasis on externalization and agnosticism. Externalization can be depicted by drawing on the “white board” feature of the virtual platform.	Drawing on a white board or piece of paper is typically done in clinic to depict externalization. This can be done on some platforms with the “white board” and/or share screen feature.	Planned (proactive adaption).	Therapeutic principles are maintained in virtual delivery.

#### Months 0–4: phase 2: creating a structure for implementation: formation of implementation teams, vFBT training, training evaluation, and full-implementation preparation

Implementation teams will be developed at each site and include program staff who are knowledgeable about the FBT model, as well as organizational processes and procedures affecting implementation. These teams will be responsible for implementing vFBT, and their leadership at the organizational level is critical for effectiveness and sustainability [27–29]. Based on our prior work, implementation teams will include a therapist, a medical practitioner, and a program administrator [28]. The Lead Principal Investigator (LPI) (JC) will meet by Zoom Healthcare with all sites to formalize implementation team membership and discuss the implementation process. Implementation teams will meet with the research team (LPI, research coordinator, and research assistant) by Zoom Healthcare on a bi-weekly basis to monitor the implementation process, discuss any issues with vFBT delivery or sustainment, and identify any further vFBT adaptations that may be necessary. Implementation teams will also be encouraged to meet on a weekly basis independent of the research team, to develop their internal capacity to manage implementation activities.

Ethics approval will be sought from each organization during this phase. Participants will be consented by our research team remotely. All therapists, medical practitioners, and program administrators will undergo vFBT training via Zoom Healthcare over a half day period to review vFBT implementation, key components of FBT to be maintained, fidelity to the vFBT model, potential barriers to success, and experiences to date. Training will be led by external experts (JL, KA) and local experts (JC, CW) who have been delivering vFBT for over 1 year related to another study (led by JL). A section of training will be devoted to how medical practitioners, and program administrators can support the implementation of vFBT within their respective roles (led by SF and PA, respectively).

#### Months 5–8: phase 3: ongoing structure once implementation begins: implementation of vFBT in practice

Phase 3 of implementation is the period during which learning becomes integrated into practitioner and program practices and therapists begin delivery of vFBT with concomitant fidelity assessment. Implementation team members will continue to participate in bi-weekly Zoom Healthcare meetings with the research team and meet weekly independent of the research team. Throughout Phase 3, therapists will recruit patients/families (with the research team obtaining consent) and will submit Zoom Healthcare videorecordings of vFBT sessions 1, 2, 3, and 4 to the research team using a secure cloud-based platform (OpenText/Hightail) for transferring large files. These sessions will be rated for fidelity by an expert in fidelity rating (JC, GD). Therapists will participate in bi-weekly group clinical consultation meetings led by vFBT Trainer LPI (JC) by Zoom Healthcare, to troubleshoot general clinical vFBT issues. Therapists at each site will be encouraged to meet independently from the research team for peer supervision on a weekly basis.

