### Research questions

Does our adaptation to vFBT maintain the key components of standard FBT by therapist self-report?Does our implementation approach for vFBT lead to implementation success at the participating sites, as measured by expert rating of fidelity to the vFBT model?What is the experience of implementation teams and patients/families implementing vFBT (and for therapists, does the experience change over time)?Do patients in vFBT demonstrate clinical outcomes similar to patients receiving standard FBT?

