#### Fidelity to the vFBT model (question 2)

Each therapist will videorecord vFBT sessions 1, 2, 3, and 4 with one patient and their family on Zoom Healthcare and submit these recorded sessions to the LPI via a secure file sharing platform for transferring large files (OpenText/Hightail). Experts in FBT fidelity rating (JC, GD) will rate the recordings using the FBT Fidelity and Adherence Check (FBT-FACT) [39, 40].

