#### Fidelity to the vFBT model (question 2)

The percentage of therapists demonstrating vFBT fidelity will be determined by the FBT fidelity rating scale (FBT-FACT [39]) rated by experts and achieving a 4/7 average score or greater on each session [40].

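### The lead principal investigator helps train the therapists, leads their consultation and is one of two raters of the fidelity score that defines implementation success, so the 4/7 percentage is open to unmasked rater bias

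*Protocol article*

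**What the plan says.** All references are to the protocol article.

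- **Role of the endpoint.** Research questions, question 2: "Does our implementation approach for vFBT lead to implementation success at the participating sites, as measured by expert rating of fidelity to the vFBT model".
- **Rule.** Analysis, Fidelity to the vFBT model (question 2): the result is the percentage of therapists meeting the FBT-FACT criterion, "rated by experts and achieving a 4/7 average score or greater on each session".
- **Raters.** Months 5–8 (phase 3): "These sessions will be rated for fidelity by an expert in fidelity rating", followed by two sets of initials. Measures, Fidelity to the vFBT model (question 2): "Experts in FBT fidelity rating", with the same two. The first set belongs to the lead principal investigator. The second rater has no training or consultation role in the article.
- **Training.** Months 0–4 (phase 2): "Training will be led by external experts", two in number, together with two local experts, one of whom is the lead investigator. The workshop covers fidelity to the vFBT model.
- **Consultation.** Months 5–8 (phase 3), the same months as the fidelity assessment: "Therapists will participate in bi-weekly group clinical consultation meetings led by vFBT Trainer LPI". The lead investigator also belongs to the research team that meets the implementation teams every two weeks.
- **Handling of recordings.** Measures tells therapists to "submit these recorded sessions to the LPI via a secure file sharing platform". Months 5–8 sends the recordings to the research team, which Months 0–4 lists as the lead investigator, the research coordinator and the research assistant.

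**The concern.** FBT-FACT is a judgement score. One of the two people who may supply it helped deliver the training, and leads the consultation, that the score is used to evaluate. The ratings are made from video, so this rater will recognise therapists met at the workshop and in consultation; no relabelling of files can mask the lead investigator to therapist or site.

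The form of the endpoint makes it sensitive to a small shift. The score is cut at 4/7, all four sessions must reach the cut-off, and the denominator is about eight. One borderline session decides a therapist's status. The other quantitative check on delivery, question 1, is therapist self-report, so the expert rating is the only external measure of whether vFBT was delivered as intended.

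**Working it through.** **Step 1. Denominator (the plan's own figure).** Sample size section: 4 programs × 2 therapists = 8, as stated. With four sessions each, 8 × 4 = 32 recordings. One reclassified therapist moves the percentage by 100/8 = 12.5 points.

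**Step 2. Precision at n = 8.** Exact (Clopper-Pearson) 95% intervals: 4/8 = 50% (16% to 84%); 6/8 = 75% (35% to 97%); 7/8 = 87.5% (47% to 99.7%). These intervals carry sampling error only and do not cover a systematic shift by a rater.

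**Step 3. Effect of a rater shift.** The article gives no mean, SD or rater difference, so all of these are assumptions. Let a session score be normal with true mean μ, between-therapist SD 0.4 and session SD 0.45, and let the rater add b points. A therapist passes if all four sessions reach 4:

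P(pass) = ∫ [Φ((μ + b + 0.4z − 4)/0.45)]⁴ φ(z) dz

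If the lead investigator rates every recording:

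| True mean μ | b = 0 | b = 0.3 | b = 0.5 | Rise in points |
|---|---|---|---|---|
| 4.2 | 31% | 53% | 68% | 23 to 38 |
| 4.5 | 53% | 75% | 85% | 22 to 32 |
| 5.0 | 85% | 95% | 98% | 9 to 12 |
| 5.5 | 98% | 99.5% | 99.8% | about 2 |

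Rises are taken before rounding the percentages.

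**Step 4. If the lead investigator rates half the therapists.** The expected percentage is the average of the b = 0 and shifted columns, so the rise halves. At μ = 4.5: (53 + 75)/2 = 64% for b = 0.3, and (53 + 85)/2 = 69% for b = 0.5.

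**Step 5. Direction.** The same formula applies to a rater who is too strict. At μ = 4.5, b = −0.3 gives 31% and b = −0.5 gives 18%.

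**Step 6. Other spread assumptions.** With a total SD of 1, means of 4.0 to 5.0 and within-therapist correlation of 0 to 0.8, a shift of 0.5 adds about 15 to 27 points and a shift of 0.25 about 7 to 14, again if one rater scores everything. For example, at mean 4.5 and correlation 0.5 the percentage goes from 40% to 63% for b = 0.5.

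**The case against.** **The evaluated approach is not one person's work.** This stands. Four people lead the workshop, others lead sections of it, and the approach also includes implementation teams and peer supervision. The lead investigator is a substantial contributor, and that is all the point needs.

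**A second rater is named.** This does not cure the problem, because nothing makes that rater's score the one that counts. A reader might infer from the singular and plural wording about raters that recordings will be split between the two, so that rater severity is confounded with therapist. The document does not support that: the plural is equally compatible with both raters scoring every session. The rating allocation, double-rating and agreement checks may well be in a fuller document, and their absence here is not the finding. The lead investigator's place among the raters is stated in the article itself.

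**Knowledge of the recorded cases.** A reader might infer that the lead investigator will have discussed these cases in consultation. The article describes group meetings on general clinical issues and does not say that recorded cases come up. Recognising the therapist is enough for the point.

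**The effect may be small.** This stands in part. Therapists must already be trained, supervised and delivering FBT, so a mean well above 4 is plausible, and at 5.5 the shift is about 2 points.

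**The stakes are limited.** This also stands. The study calls itself a feasibility and pilot study, the percentage is descriptive, no test or go/no-go rule depends on it, and it answers one of four questions.

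**Conclusion.** The point holds as a statement of exposure to bias. The article places the lead principal investigator among the trainers, as leader of consultation, and as one of two raters of the score that defines implementation success. It does not show that scores will be inflated; neither size nor direction can be derived from it.

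Under the stated SDs and a leniency of 0.3 to 0.5 points, the effect runs from about 2 points (mean 5.5) through 9 to 12 (mean 5.0) to 22 to 32 (mean 4.5), or half of each if the lead investigator rates half the therapists. Quoting only the near-threshold, all-recordings case would overstate it.

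This is a should-fix. A reader might treat it as fatal to question 2, but a descriptive percentage in about eight therapists already supports only loose inference. It still deserves action because the bias is avoidable and, once ratings are made, can be removed only by re-rating.

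**What to change.** 1. Base the question 2 percentage on the second named rater's scores for all of the roughly 32 recordings, rated in random order. First confirm that this rater has no training or consultation role with the sites; the article states none, which is not proof of none.
2. Use the lead investigator's ratings only on a subset, for example one recording per therapist (8), to report agreement as an ICC and the mean rater difference.
3. Reconcile the two statements on who receives the recordings (the research team in Months 5–8, the lead investigator in Measures). Have the research coordinator receive and label the files.
4. If the second rater cannot take all recordings, report the percentage by rater and state the lead investigator's dual role as a limitation.

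**Cost.** More rating time for the second rater, whose capacity the article does not show. The plan needs no new staff if that capacity exists. According to Trial status, staff consent and workshop preparation are under way and no data have been cleaned or analysed, so the change can be made before any session is rated.

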#### Months 9–12: phase 4: improving future applications: evaluating the experience of the implementation intervention

The evaluation phase of our implementation approach will involve the solicitation of feedback about the overall implementation process and a consideration of any further adaptations to the vFBT model that may be necessary for effective and sustained use over time. Implementation teams will continue to meet on a weekly basis without the research team, and therapists will continue to meet on a weekly basis for peer supervision, without the research team. One focus group will be completed at each organization, involving the participating therapists, medical practitioner, and program administrator. Focus group questions will elicit user experiences of the implementation process, perceptions about implementation success, and areas needing further adaptation. Semi-structured qualitative interviews will also be completed with patients and their families to elicit their perceptions of virtual treatment. Quantitative measures will also be evaluated, as described below.

### Measures

#### Key components of FBT (question 1)

Each therapist will submit a self-report questionnaire entitled the Key Measures of Therapist Behaviours and Self-Efficacy in FBT (developed by JL) as an indicator of their adherence to the key components of standard FBT within the vFBT model. This questionnaire will be completed after session 4 of vFBT and will be submitted using an online survey tool (Qualtrics).

#### Fidelity to the vFBT model (question 2)

Each therapist will videorecord vFBT sessions 1, 2, 3, and 4 with one patient and their family on Zoom Healthcare and submit these recorded sessions to the LPI via a secure file sharing platform for transferring large files (OpenText/Hightail). Experts in FBT fidelity rating (JC, GD) will rate the recordings using the FBT Fidelity and Adherence Check (FBT-FACT) [39, 40].

#### Implementation team and patient/family experiences of vFBT (question 3)

The experiences of therapists, medical practitioners, and program administrators implementing vFBT across settings will be evaluated qualitatively using the method of fundamental qualitative description [41]. We will ask participants at each site to undergo a semi-structured focus group with a member of our research team which will be recorded using Zoom Healthcare. These qualitative evaluations will focus on the execution of the implementation process, and the overall perceived success of the implementation. Patients/families will also participate in a semi-structured qualitative interview to share their experience of vFBT. A similar process of videorecording, transcription, and analysis will occur for focus groups and for family interviews.

In addition to these qualitative methods, quantitative measures will be collected from therapists to examine their change in readiness, attitudes, and confidence for virtual treatment delivery over time. Therapist individual readiness for change will be evaluated using the Brief Individual Readiness for Change Scale (BIRCS) [42], their attitudes about evidence-based practice will be assessed using the Evidence Based Practice Attitudes Scale (EBPAS) [43], and confidence related to the intervention will be assessed by administering an adapted version of the Perceived Attributes of the Principles of Effectiveness Scale (MPAS) [44]. These measures will be delivered at implementation baseline (at the time of consent), immediately following the vFBT training workshop, and after session 4 of vFBT has been completed (all by Qualtrics). These measures will help us evaluate any change in readiness, attitudes, and confidence over time so that we can better understand therapist experiences with the implementation approach. Therapist, medical practitioner, and program administrator demographics will also be collected at implementation baseline (at the time of consent).

#### Patient outcomes (question 4)

Patient outcomes including weight and number of binge/purge episodes per week will be recorded at treatment baseline (at the time of patient consent) and then submitted on a weekly basis after each of the first four vFBT sessions by the therapist (using Qualtrics). Weight gain of at least 2 kg following the first four sessions of FBT is highly predictive of final treatment outcome [45, 46] and is a valid measure of overall clinical effectiveness. This will be our benchmark for comparing vFBT effectiveness to standard FBT. Patient demographics and diagnosis will be collected at treatment baseline (at the time of patient consent).

